# List of used acronyms and abbreviations

| **Abbreviation** | **Term/Explanation** |
| --- | --- |
| ACE2 | Angiotensin-converting enzyme 2 |
| AE | Adverse Event = any untoward medical occurrence |
| AR | Adverse Reaction = adverse event, that is each unfavorable and unexpected reaction to a study treatment, regardless of dose |
| CNS | Central nervous system |
| CRF | Case Report Form |
| DSMB | Data Safety Monitoring Board |
| DSUR | Development Safety Update Report = annual safety report |
| EPM | Etikprövningsmyndigheten (English: Swedish Ethical Review Authority) |
| GCP | Good Clinical Practice |
| ICH | International Council for Harmonization |
| ICU | Intensive care unit |
| ITT | Intention-to-treat = including all data from all subjects who have participated in the study |
| LVFS | Läkemedelsverkets författningssamling (English: Swedish Medical Products Agency’s statutes) |
| MPA | Swedish Medical Products Agency |
| PCR | Polymerase chain reaction |
| PP | Per Protocol analysis = including only data from subjects who have completed the study completely in accordance with the protocol, with no deviations from the protocol |
| SAE | Serious Adverse Event = serious untoward medical occurrence |
| SPC or SmPC | Summary of Product Characteristics |
| SUSAR | Suspected Unexpected Serious Adverse Reaction |
| TMPRSS2 | Transmembrane protease, serine 2 |

# Synopsis

| EudraCT number: | 2020-002027-10 |
| --- | --- |
| Title: | A prospective, multicenter, randomized PHASE II clinical trial of enzalutamide treatment to decrease the morbidity in patients with Corona virus disease 2019 (COVID-19). |
| Study code: | COVIDENZA |
| Short background/ Rationale/Aim: | COVID-19 is a disease with high rate of morbidity if symptomatic. There is a great need of treatments to decrease the symptoms, time at hospital and need of intubated mechanical ventilation. The majority of patients needing intensive care are men. This may be due to the androgen regulation of TMPRSS2 or ACE2, necessary for virus internalization, or immune response. Enzalutamide is an antiandrogen inhibiting the activation of androgen receptors and its downstream events such as gene expression or immune cell activity. The aim of this trial is to evaluate a possible beneficial effect of short-term enzalutamide treatment of COVID-19 patients. |
| Study objectives: | Primary objective:   - Clinical status as assessed by the 7-point ordinal scale up to 30 days after inclusion   Secondary objectives:   - Safety evaluation, as measured by AEs, Adverse Reactions (ARs), SAEs, Serious ARs (SARs) - Duration of supplemental oxygen (days) - Need of mechanical ventilation - Laboratory assessment day 0, 2, 4 and 6 - Virus load assessment day 0, 2, 4 and 6 - Hospital stay (days) - Re-admission to hospital due to rebound COVID-19 - Mortality at 6 months - Hormonal status at 6 months - Serological immunity for COVID-19 at 6 months |
| Study design: | The trial is a non-blinded randomized multicenter clinical trial designed to compare the outcomes between arm 1 (experimental arm) and arm 2 (control arm) by the ratio 2:1.  Arm (1) (experimental arm):  • Enzalutamide 160mg once daily (4x40mg tablets) for 5 days + Standard of care  Arm (2) (control arm)  • Standard of care |
| Study population: | Patients with COVID-19 with mild to severe disease of the age of 50 or above. |
| Number of subjects: | N=45 (explorative phase)  N= Up to 100 (prolongation phase)  N= Up to 600 (full trial) |
| Inclusion criteria: | - Positive COVID-19 test - Mild to severe symptoms of COVID-19 - Recent hospitalization due to COVID-19 (0-3 days) - WHO performance status 0-3 - Age above or equal to 50 years - Can understand all the requirements of the study, provide informed consent, and provide authorization of use and disclosure of personal health information. - Estimated expected survival of 1 year (excluding symptoms due to COVID-19) |
| Exclusion criteria:   - Severe allergy to Enzalutamide - Pregnant or breast-feeding women - Need of immediate mechanical ventilation - Current hormonal treatment for prostate or breast cancer (finasteride and dutasteride are allowed) - Treatment for HIV - Treatment with warfarin or Clopidogrel - Treatment with immunosuppressive agents. Allowed exceptions are: equivalent medication to prednisolone 10 mg/day or low dose methotrexate 15 mg/week. Any treatment initiated as standard of care for COVID-19 is allowed. - Severe immunosuppressive disease - Stroke in medical history - Epileptic seizure in medical history - Other serious illness or medical condition - Current symptomatic unstable cardiovascular disease | |
| Investigational product(s), dosage, administration: | Enzalutamide film-coated tablets 4 x 40 mg (160mg) once daily for 5 days, per oral administration |
| Study endpoints: | Primary endpoints (variable):  **Time to need of mechanical ventilation or death**, and **time to discharge** as assessed by the 7-point ordinal scale up to 30 days after inclusion,  1) Not hospitalized, no limitations on activities.  2) Not hospitalized, limitation on activities;  3) Hospitalized, not requiring supplemental oxygen;  4) Hospitalized, requiring supplemental oxygen;  5) Hospitalized, on non-invasive ventilation or high flow oxygen devices; 6) Hospitalized, on invasive mechanical ventilation or extracorporeal membrane oxygenation (ECMO);  7) Death;  Secondary endpoint(s) (variables):  Safety evaluation, as measured by AEs, Adverse Reactions (ARs), SAEs, Serious ARs (SARs) :  30 days evaluations  Duration of supplemental oxygen (days):  Total days of extra oxygen.  Need of mechanical ventilation:  Evaluated for 30 days and after 6 months.  Laboratory assessment:  Hb, LPK, B-lymphocytes, CRP, IL-6, ASAT, ALAT, ALP, creatinine, D-dimer  Virus load assessment:  PCR based SARS-CoV-2 measurement from upper respiratory tract  Hospital stay (days)  Evaluated for 30 days and after 6 months  Re-admission to hospital due to rebound COVID-19  Evaluated for 30 days and after 6 months  Mortality at 6 months  Death due to any cause  Hormonal status at 6 months  FSH, LH, SHBG, testosterone and estrogen levels |
| Study period: | Q2 2020-Q2 2022 |

# Background and rationale

# SUMMARY

COVID-19 is a disease with high rate of morbidity if symptomatic. There is a great need of treatments to decrease the symptoms, time at hospital and need of intubated mechanical ventilation. This randomized trial will evaluate the effect of short-term enzalutamide treatment to decrease the need of worsening of the disease.

# Background

The pandemic outbreak of Sars-CoV-2 leads to high mortality and a huge burden for the health care system. To date over 2 million people have been confirmed with COVID-19 and more than 133,000 deaths have occurred (April 15^th^, Worldometers.info). Global epidemiological data shows an over-representation of men among those more severely affected and among deaths. The published data from Sweden supports this, despite showing equal risk of being diagnosed with COVID-19 for men and women, there is an increased risk of need for intensive care and risk of death for men compared to women (Folkhälsomyndigheten and SIR – intensivvårdsregistret). Of the patients in need of intensive care, about 75% are men (765 men vs 259 women (April 17^th^, Folkhälsomyndigheten).

The reason for this discriminating action of Sars-CoV-2 has, so far, not been explained. Smoking, which has been identified as a contributing risk factor for more severe disease, may be more frequent among men in some countries but in Sweden the smoking habits among men and women are similar (16% smokers among men, and 14% among women. Metabolic syndrome, conferring risk factors such as high blood pressure, obesity, and diabetes (type 2), is more frequent among men in Sweden but the difference is rather small (approximately 24% of men and 19% of women), which is not likely to explain the large difference in the response to the Sars-CoV-2 virus. However, one obvious difference between men and women is the testosterone level. A recent epidemiology study from Italy supports the notion that testosterone may influence SARS-COV-2 infection showing that prostate cancer patients on medical castration was much rarely infected compared to other male cancer patients (Montopoli et al. Ann Oncol. 2020).

It has recently been demonstrated that the Sars-CoV-2 virus employs the transmembrane protease, serine 2 (TMPRSS2) for S protein priming necessary for internalization into the cells after binding to the angiotensin-converting enzyme 2 (ACE2), and a TMPRSS2 inhibitor blocked virus entry into lung cells in vitro (Hoffman et al. Cell 2020). In a TMPRSS2 knockout mouse model, mice infected with the H1N1 influenza virus (which also uses the TMPRSS2 protein for its entrance) displayed less infection and an attenuated disease course with less lung pathology, weight loss, and mortality, compared to wild-type control mice (Hatesuer *et al*. PLoS Pathog 2013).

# Benefit-risk evaluation

### Potential benefits for study participants

The pre-clinical studies show that TMPRSS2 down-regulation deteriorate the possibility for the SARS-CoV-2 to infect the lung cells, due to the strong regulation of TMPRSS2 by the androgen receptor the effect of enzalutamide treatment may eradicate further replication of the virus into new lung cells with in 24 hours after enzalutamide treatment. The benefit for the patients receiving enzalutamide may lead to both shorter time at hospital with less morbidity, lower risk of transfer to ICU and lower risk of death due to COVID-19. The strong overweight for men at the ICU may be due to the higher levels of testosterone, and if the risk of ICU care would diminished to the same levels as for women this will be of great benefit for the patients and the health care system. In women this mechanism may be as important and the benefit of decreasing the number of women to have increased morbidity and/or admission to ICU would be of great benefit for the patients and the health care system.

Further if enzalutamide is beneficial for the course of the disease, this may minimize the time at hospital and risk of sequelae for the individual patient due to no need for invasive mechanical ventilation.

Further this may be beneficial for other patient in need of the space limited ICU clinics and the stress on the health care system during the pandemic COVID-19 outbreak. The costs and stress for the COVID-19 pandemic is huge and any lessening of the burden can be of pivotal importance.

### Potential risks for study participants due to enzalutamide treatment

Enzalutamide is a potent androgen receptor inhibitor with effect on many organs including muscles, central nervous system (CNS), reproductive organs and the immune system. Even though enzalutamide is well tolerated and has few serious side effects there is an increased risk of some side effects related mostly to the CNS effects. The trials have been performed in men taking enzalutamide for sometimes many years and in many cases in metastatic prostate cancer.

The reported common side effects in both treated men and women include headache, amnesia, asthenia, tiredness, restless legs, anxiety and hot flushes. The more severe side effects include seizure (the incidence was 0.4% (13 of 3179 men) in the enzalutamide arm compared to 0.1% in the placebo arm of the combination of the trials). In the registration trials there was a small increased risk of ischemic heart disease of 2.5% compared to 1.4% in the placebo arm. The DSUR side effect report to the Swedish Medical product agency (DSUR_31AUG2018), states in the accumulated analysis: “Taken together, the non-clinical and clinical data suggest that enzalutamide is not associated with an increased risk of QT prolongation, ischemic heart disease, heart failure or arrhythmias”.

There are some possible interactions with other drugs due to induction of many cyp-enzymes which has led to exclusion criteria (below) and a notification to the clinics to be aware of and adjust the doses of Azitromycin and omeprazole.

The effect on the desire and potency due to androgen signaling inhibition of enzalutamide is known but is reversible. The effect by enzalutamide on the bone-homeostasis after long time treatment and breast tissue (especially on men) after a couple of months treatment, leading to osteoporosis and gynecomastia, respectively, are unlikely to be seen in the short-term treatment. Interactions of Enzalutamide with other medicinal products are mostly due to liver enzyme induction and may also be of less importance due to the short time of treatment. To minimize this risk we will exclude patients using medicinal products known to interact with the enzalutamide treatment.

For updated SPC see Fass.se (<https://www.fass.se/LIF/product?userType=0&nplId=20160310000078>)

The patients with COVID-19 disease with mild to severe symptoms may experience other side effects compared to the subject previously treated with enzalutamide.

The effect on immune system is poorly investigated and the potential risks that enzalutamide may interact with the immunological response to COVID-19 course cannot be ruled out and the first explorative part of the trial will be primarily be focusing in identifying any negative effect of the treatment on the course of the disease.

The same may be true for the CNS effect of enzalutamide that may affect the symptoms and this may lead to tiredness and anxiousness. This may be giving negative effect on the patient´s wellbeing and this may lead to a worse clinical evaluation of the patients not due to the course of the disease but due to any side effect of the enzalutamide. This can of course not be ruled out fully and even though the inclusion of laboratory parameters and virus load will be initially frequently evaluated in the first phase of the trial these symptoms may lead to more intensive treatment than needed if without enzalutamide.

Interaction of Enzalutamide with medication needed for the medical care may appear. This risk has been taken care of by excluding patients using medicine known to be affected by the enzalutamide treatment.

In summary, the side effects and interactions are well documented for enzalutamide and can be taken care of and the risk of any persistent side effect is minimized by the short-term treatment and frequent safety monitoring.

The risk of experiencing inconvenience by the study related procedures, including assessment of the clinical parameters, the clinical laboratory tests and the evaluation of hospital stay, 7-point ordinal scale and follow up after 6 months before the end of the trial.

The risk for the research personal and monitors in the trial to be exposed to the COVID-19 disease will be mitigated by having protocol for handling of any contaminated source data and/or forms. This will be handled according to suggested alternatives for below.

### Equipoise

Since the side effect profile of enzalutamide is considerably less harmful than the natural course of COVID-19 morbidity in hospitalized patients, the overall risk assessment is beneficial for testing enzalutamide to improve the outcome of COVID-19.

The possibility that enzalutamide may decrease the burden for the health care system may be indirectly more important than the effect on the individual patient, due to the limited capacity of the ICU clinic and health care personal, that leading to displacement effect for other diseases with mortality and morbidity.

The enzalutamide treatment is used in elderly patients in prostate cancer above 80+ and in this age the side effects seem to be few. If enzalutamide may be beneficial for the COVID-19, enzalutamide may be a great option to decrease the mortality in patients in elderly home with very little negative effects of the medicine.

# Study objectives

## Primary objective

The primary objective of this study is to evaluate the effect of enzalutamide treatment to the changes in morbidity and mortality in the course of COVID-19 in comparison to standard of care.

## Secondary objective(s)

The secondary objectives of this study are to evaluate the safety of enzalutamide treatment in COVID-19 patients, gender difference in the treatment efficacy, and evaluate serological immunity to COVID-19 in enzalutamide treated persons compared to standard of care.

## Primary endpoint (variable)

Primary endpoints (variables):

Time to need of mechanical ventilation or death, as a part of the clinical status as assessed by the 7-point ordinal scale up to 30 days after inclusion.

Time to discharge from hospital, as a part of the clinical status as assessed by the 7-point ordinal scale up to 30 days after inclusion

1) Not hospitalized, no limitations on activities.

2) Not hospitalized, limitation on activities;

3) Hospitalized, not requiring supplemental oxygen;

4) Hospitalized, requiring supplemental oxygen;

5) Hospitalized, on non-invasive ventilation or high flow oxygen devices;

## 6) Hospitalized, on invasive mechanical ventilation or extracorporeal membrane oxygenation (ECMO); 7) Death; Secondary endpoint (variables)

Safety evaluation, as measured by AEs, Adverse Reactions (ARs), SAEs, Serious ARs (SARs):

Frequency and type of “adverse reaction form” evaluated during 45 days.

Duration of supplemental oxygen (days):

Total days of extra oxygen.

Need of mechanical ventilation:

Evaluated for 30 days and after 6 months.

Laboratory assessment:

Hb, LPK, B-lymphocytes, CRP, IL-6, ASAT, ALAT, ALP, Krea, D-dimer

Virus load assessment:

PCR based SARS-CoV-2 measurement from upper respiratory tract

Hospital stay (days)

Evaluated for 45 days and after 6 months

Re-admission to hospital due to rebound COVID-19

Evaluated for 45 days and after 6 months

Mortality at 6 months

Death due to any cause

Hormonal status at 6 months

FSH, LH, SHBG, testosterone and estrogen levels

Serological immunity for COVID-19 at 6 months

Serum blood sample will be analyzed centrally for antibodies against Sars-CoV2.

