### Explorative phase:

During the first phase (explorative) 45 patients will be included. Extended testing to identify changes in virus load will be performed to identify any differences between the arms and between gender. This phase is further important to identify any serious adverse event related to enzalutamide treatment in COVID-19 patients.

During this phase the DSMB will have a weekly report from the statistician and give a report to the steering group.

If safety and possible positive effect of enzalutamide for COVID-19 from the first phase may be beneficial and if the DSMB approve to move the trial into the prolongation phase. If needed the inclusion criteria may change to include only one gender or other changes in discussion with DSMB and steering group. Any changes to the protocol will be sent in as amendment to the Swedish Medical Products Agency (MPA) and ethical committee before the inclusion can go beyond 45 patients.

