**Virus load assessment:**

PCR based SARS-CoV-2 measurement from upper respiratory tract.

The tests will be handled in the clinic where the patients is admitted at day 0, 2, 4 and 6. If the patient is discharged before day 6, the last test will be taken at the day of discharge.

Only the relative change of the PCR will compared for the patient and therefore the PCR will be performed at the same day after all sample have been collected at the labs used by the local clinic where the samples has been taken, or transferred to a central study laboratory

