### Secondary objectives

Frequencies of Adverse events will be compared between the two arms using Fisher’s exact test.

Duration of supplemental oxygen (days) will compared between study arms using linear regression adjusted for gender and site.

Time to need of mechanical ventilation will be compared using the ordinal scale, between study arms using Cox regression. And the frequency of need of mechanical ventilation in the two arms will be tested using Fisher’s exact test.

Laboratory assessments at each time of measurement will be compared to baseline and extreme value and differences between study arms evaluated using linear or generalized linear regression adjusting for site, age and gender.

The change in viral load on day 2, 4 and 6 as compared to baseline will be compared between study arms. Also, the maximum decrease in viral load will be calculated, as the difference between observed value and maximal observed value, and compared between study arms. The analyses will be performed using linear regression adjusting for site and gender.

Total hospital stay (days) evaluated at 30 days and 6 months will be compared between groups using linear regression adjusting for site, age and gender.

Frequency of re-admission to hospital due to rebound COVID-19 will be compared between study arms using Fisher’s exact test.

Time to death will be compared between study arms using Cox regression adjusting for site and gender.

Hormonal status at 6 months will be compared to normal reference values and compared between study arms.

Frequency of serological immunity for Covid-19 will be compared between the study arms using Fisher’s exact test.

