### Drop-outs

In all survival analyses drop-out will be censored at time of drop-out. For all other analyses drop-outs will be excluded from the analyses.

- 1. Adjustment of significance and confidence interval

Indicate possible tests for multiple comparisons. Adjustment should always be considered for multiple primary outcomes. Specify details of any adjustment procedures or provide an explanation for why justification is not considered necessary.

Multiple testing correction will be performed using Bonferroni’s methods to adjust for having two primary outcomes.

- 1. Sample size calculations

The sample size of the full study will be determined based on data from the prolongation study.

- 1. Interim analysis (if relevant)

The primary outcomes will be evaluated after prolongation phase.

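### Linear regression on change in PCR viral load cannot represent undetectable swabs; if these are set to the limit or dropped, the arm difference is biased toward zero by an amount the protocol does not let one fix

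*Protocol*

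**What the plan says.** The secondary endpoint list names the measure only: "PCR based SARS-CoV-2 measurement from upper respiratory tract". Section 8.1.2 sets swabs on days 0, 2, 4 and 6 and adds that "Only the relative change of the PCR will compared for the patient". It does not say whether that means log10 load, cycle threshold (Ct) or something else.

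Section 10.2.1 (Secondary objectives) fixes variables and model:
- "The change in viral load on day 2, 4 and 6 as compared to baseline will be compared between study arms".
- A second variable: "the maximum decrease in viral load will be calculated, as the difference between observed value and maximal observed value".
- For both: "The analyses will be performed using linear regression adjusting for site and gender". Day-0 load is not among the covariates.

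The Drop-outs paragraph says "For all other analyses drop-outs will be excluded from the analyses". That concerns patients who leave the trial, not swabs below a detection limit. No section gives a detection limit or a rule for an undetectable result.

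The section on the explorative phase gives the endpoint a purpose: "Extended testing to identify changes in virus load will be performed to identify any differences between the arms and between gender".

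**The concern.** An undetectable swab is known only to lie below the assay's limit. Linear regression needs a number for each observation, so the swab must be given a value or be left out. Setting it to the limit caps the recorded fall. Leaving it out removes patients who did best. If enzalutamide speeds clearance, more treated than control swabs reach the floor, so the distortion grows with the true effect.

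Viral load is the most direct test in the trial of the TMPRSS2 mechanism, and looking for arm and gender differences in it is a stated aim of the first 45 patients. After that phase the protocol allows inclusion to be narrowed to one gender. An attenuated estimate could be read as little antiviral activity.

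**Working it through.** **Plan's own figure.** There is none to reproduce: the protocol states no effect, SD, limit, undetectable share or power for viral load. From the protocol come the variable, the model, 2:1 allocation, and phases of 45, 100 and up to 600 patients. Everything else below is assumed. Site and gender are left out of the calculations.

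**1. Undetectable swabs set to the limit.** Assume follow-up log10 load is normal with mean μ and SD σ, limit L, and all baselines detectable. The recorded mean is

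E[max(Y, L)] = L·Φ(a) + μ·(1 − Φ(a)) + σ·φ(a), with a = (L − μ)/σ.

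Baseline has the same expectation in both arms, so the arm difference in change equals the arm difference in this mean.

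Example with L = 0, σ = 2.0, true effect 0.5 and 20% of controls undetectable:
- Control: μ = 0.8416 × 2.0 = 1.683; recorded mean 1.683 × 0.80 + 2.0 × 0.280 = 1.907.
- Treated: μ = 1.183, 27.7% undetectable; recorded mean 1.183 × 0.723 + 2.0 × 0.335 = 1.525.
- Difference 0.381 instead of 0.5; shrinkage 1 − 0.381/0.5 = 24%.

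Over σ = 1.5 to 2.0 and true effects of 0.5 to 1.0 log10:

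| Controls undetectable | Shrinkage, set to limit |
|---|---|
| 2% | 3-5% |
| 10% | 12-18% |
| 20% | 24-31% |
| 30% | 35-43% |
| 40% | 45-53% |
| 60% | 65-72% |

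The substituted value matters. Placing undetectable swabs 1 log10 below the limit (effect 1.0) gives 1-4% shrinkage at 10% undetectable, 8-11% at 20% and 27-30% at 40%.

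**2. The stated variable, simulated.** Assume day-0 log10 load with mean 5 and SD 1.5, residual SD 1.3, limit 2, true extra decline 0.5, and 400:200 patients (the maximum of 600 at 2:1). About 41% of control and 50% of treated swabs are undetectable.

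| Analysis | Estimate (true 0.50) | Power |
|---|---|---|
| Linear, change, set to limit | 0.27 | 79% |
| Linear, change, dropped | 0.37 | about 82% |
| Linear, set to limit, day-0 load added | 0.28 | 92-93% |
| Tobit on follow-up load, no day-0 load | not quoted | 76-77% |
| Tobit with day-0 load | 0.49 | 97% |

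Shrinkage is 1 − 0.27/0.50 = 46% at the limit and 1 − 0.37/0.50 = 26% when dropped.

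The 46% agrees with step 1, since the follow-up SD here is √(1.5² + 1.3²) = 1.98.

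The 26% also fits. If follow-up loads alone were compared, dropping would cost 61% at this SD and effect with 40% of controls undetectable. Only 1.3²/(1.5² + 1.3²) = 1.69/3.94 = 0.43 of that selection carries into the change, and 0.43 × 61% = 26%.

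**3. Fewer undetectable swabs.** At about 23%/30%, the stated model with values at the limit has 96-98% power, Tobit without day-0 load 73-75%, and Tobit with day-0 load 97-99%. The power gain has gone; the bias remains (about 0.36 for a true 0.5).

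**4. Explorative-phase size.** At 30:15 with true effect 1.0 and about 40%/60% undetectable, the stated model (set to limit) has 23-30% power and Tobit with day-0 load 55-58%.

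**5. No effect.** At 67:33 with zero effect, rejection rates were 4% (set to limit), 4% (dropped) and 6% (Tobit), so type I error is not at issue.

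**The case against.** The strongest reply is that coding of results below a detection limit normally sits in the analysis plan, which is not shown. That stands for the coding rule: its absence is no fault. It does not dispose of the point, because the protocol goes further and names the model. An analysis plan that used a censored-data method would depart from section 10.2.1; one that followed it would have to assign or discard values.

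Three stronger readings are tempting and unsupported.
- A reader might infer that patients who clear virus are dropped. Nothing says so, and the drop-out rule does not cover them.
- A reader might state a loss of a quarter to a half as fact. With values set to the limit, that needs roughly 20-40% of controls undetectable, and the protocol gives no such share. Its remark that replication may be less prominent concerns the intensive care phase, whereas patients enter within 0-3 days of hospitalisation with a positive test.
- A reader might attribute the whole power loss to ignoring censoring. Much of it comes from leaving out day-0 load: adding that to ordinary regression lifts power from 79% to 92-93% in step 2. When follow-up loads were compared without baseline at N = 45 and N = 100, linear regression at the limit came within about 4 points of Tobit. The bias is a different matter: adding day-0 load to linear regression leaves the estimate at 0.28.

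It is also true that viral load is secondary and enters neither the primary analyses nor the sizing of the full trial.

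**Conclusion.** The point holds as a conditional one. The model fixed in section 10.2.1 has no place for an undetectable swab, and where such swabs occur and are set to the limit or dropped, the arm difference is biased toward zero. With values set to the limit, shrinkage is roughly 15% at about 10% undetectable controls, 25-30% at about 20% and 45-50% at about 40%. These figures rest on normal log10 loads, detectable baselines and assumed SDs and effects; with few undetectable swabs the harm is small. The damage is first to the size of the estimate. Power suffers mainly when many swabs are undetectable. Type I error and the primary endpoints are untouched. The change is worth making because viral load is a stated purpose of the explorative phase.

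**What to change.** In section 10.2.1, replace linear regression for viral load with censored (Tobit) regression of log10 load, or Ct, on days 2, 4 and 6, with day-0 load, site and gender as covariates. Treat undetectable results as censored at each laboratory's limit (on the Ct scale, at the upper cycle limit), never as missing. Report patients undetectable on day 0 separately: they cannot show a decline, and they may occur because any clinically used test qualifies for entry.

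Day-0 load must be in the model. Without it, power fell below that of the stated analysis (76% against 79%, and 73% against 98% with fewer undetectable swabs). Tobit on the change without day-0 load is not a safe substitute either: where decline depended on baseline it gave up to 1.30 for a true 1.0, against 0.93-1.06 with day-0 load included.

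The cost is about one sentence in the protocol and a detection limit from each laboratory, with no new samples, visits or patients. The downside is reliance on roughly normal log loads, which should be checked.
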